# Effectiveness and safety of thread embedding acupuncture for facial nerve palsy sequelae: a protocol for a multicenter, assessor-blinded, randomized, controlled clinical trial

**DOI:** 10.3389/fneur.2025.1668688

**Published:** 2025-11-12

**Keywords:** facial nerve palsy, thread embedding acupuncture, Facial Disability Index, facial stiffness, synkinesis, randomized controlled trial

## Abstract

**Introduction:**

Facial nerve palsy can result in various sequelae. Recent reviews and clinical studies reported that thread-embedding acupuncture is a safe treatment and can improve facial nerve palsy sequelae. This trial aims to confirm the effectiveness and safety of thread-embedding acupuncture for patients with facial nerve palsy sequelae.

**Methods:**

A multicenter, randomized, assessor-blinded clinical trial will be conducted. One hundred forty-two participants will be recruited by eligibility criteria and be randomly divided into two groups. The intervention group will receive thread-embedding acupuncture in addition to electroacupuncture, while the control group will be given only electroacupuncture. The primary outcome is a change in the physical function score of the Facial Disability Index. The secondary outcome is change in Sunnybrook Facial Grading System, Social/Wellbeing function score of Facial Disability Index, Synkinesis Assessment Questionnaire, Numeric Rating Scale of stiffness by facial region, Patient Global Impression of Change, Euro-Qol 5-Dimension 5-level, Economic evaluation questionnaire and adverse events. Assessment points include before treatment (Week 1), after treatment completion (Week 6), 2 weeks post-treatment completion (Week 8, Primary endpoint), and 10 weeks post-treatment completion (Week 16).

**Conclusion:**

This randomized controlled trial will assess the effectiveness and safety of thread-embedding acupuncture treatment alongside electroacupuncture for facial nerve palsy, using proper sample sizes and rigorous methodologies to address previous research limitations.

**Clinical trial registration:**

https://cris.nih.go.kr/cris/search/detailSearch.do?seq=25846&status=5&seq_group=24726&search_page=M, identifier KCT0008551.

## Introduction

1

Facial nerve palsy (FNP) is an acute palsy that appears on the face, with an incidence of approximately 20–25 cases per 100,000 people annually. It involves partial or complete loss of facial movement, accompanied by symptoms such as taste abnormalities in the front part of the tongue, hypersensitivity of hearing, tinnitus, and postauricular pain. Although most cases of FNP recover usually, some may result in sequelae (1). The progress of FNP shows that approximately 71% of patients can fully recover without treatment within 6 months; however, 29% may experience residual sequelae (2). The sequelae of facial palsy typically manifest about 3–6 months after onset and can include synkinesis, contracture, spasm, and crocodile tears syndrome. The prevalence of specific sequelae symptoms is as follows: contracture in 17%, synkinesis in 16%, crocodile tear syndrome in 2%, and ocular dryness in 2% (3).

Long-term sequelae of FNP can make it difficult for patients to express themselves through facial gestures, leading to discomfort in daily life and professional activities due to facial deformities, stiffness, and irregular movements. Furthermore, these facial changes can result in a decline in self-confidence and self-esteem, causing patients to hesitate to engage with others and encounter difficulties in social activities (4).

While the acute phase treatment of facial palsy is well standardized, only two approaches, nerve transplantation, and botulinum toxin treatment, are known for treating post-sequelae. Furthermore, due to limited evidence supporting these methods, patients are only offered restricted options (5). Consequently, there has been a growing interest in non-surgical therapies using complementary and alternative medicine (6). Recently, thread-embedding acupuncture (TEA) has been utilized in treating FNP. TEA is a method in which an external material is embedded within the acupoint. This material can be used to continuously stimulate the meridian and consequently treat diseases (6). According to a systematic review on the safety of TEA reported in 2021, an examination of 45 randomized controlled trials and 16 case reports revealed that TEA is a very safe treatment. Notably, no serious adverse events occurred when using polydioxanone thread material predominantly utilized in Korea (7). Additionally, a review of clinical reports from Korea on facial thread embedding treatment revealed that, apart from mild cases of bruising, there were no significant side effects, making it a relatively safe treatment (8).

In 2020, we reported the results of a clinical trial comparing TEA with sham TEA for the FNP sequelae. Although we could explore the clinical potential of TEA for the FNP sequelae, since this was the first clinical trial conducted, several limitations were found in the study design (9). To overcome these limitations, this clinical trial aims to confirm the effectiveness and safety of the FNP sequelae depending on whether or not TEA is performed based on full-scale design, appropriate sample calculation, and comparison similar to clinical situations.

## Methods

2

### Trial design

2.1

This protocol was designed according to the standard protocol items: recommendations for interventional trials (SPIRIT) checklist and Standards for Reporting Interventions in Clinical Trials of Acupuncture (STRICTA) 2010 checklist of information to include when reporting interventions in a clinical trial of thread embedding. The study protocol (FTEA-2023-01, version: 1.5) was approved by the Institutional Review Board (IRB) of the Kyung Hee University Oriental Hospital at Gangdong (Approval Number: KHNMCOH IRB 2022-09-001) and the Pusan National University Korean Medicine Hospital (Approval Number: PNUKHIRB 2022-09-003). Additionally, this study was registered in the Clinical Research Information Service (KCT0008551). If there are any changes in the study design, the Ethics Committee will be immediately informed.

This study will be a multi-center, randomized, assessor-blinded clinical trial with a single treatment (TEA). A total of 142 participants with FNP sequelae more than 12 months after onset will be recruited from the Kyung Hee University Oriental Medicine Hospital at Gangdong and the Pusan National University Korean Medicine Hospital. Detailed information regarding the study will be provided to all potential participants beforehand, and only those who agree to participate and sign an informed consent form will undergo eligibility screening. Those who meet the inclusion and exclusion criteria will be randomly assigned to the TEA or control groups. The study will consist of a screening period, six treatment sessions (Week 1–6) over 6 weeks and two additional follow-up sessions (Week 8 and 16), and will be conducted according to the designated scheduled appointment. The trial design is summarized in Figure 1. Table 1 shows more details regarding the SPIRIT schedule for enrollment, interventions, and assessments. The enrollment is expected to begin on June 22, 2023 and end on July 31, 2025. Data collection is scheduled to be completed by November 30, 2025, with preliminary conclusions expected to be drawn by December 31, 2025.

**Figure 1 fig1:**
[figure not shown]
Flow chart of the study.

**Table 1 tab1:** SPIRIT schedule of the study.

Timepoint	Study period					
	Screening	Allocation and enrollment	Post-allocation		Follow-up	
		Week 1 (Baseline)	Week 2–5	Week 6	Week 8 (Primary endpoint)	Week 16
Visit		Visit 1	Visit 2–5	Visit 6	Visit 7	Visit 8
Visit window			±3	±3	±3	±7
Enrollment						
Informed consent	O					
Eligibility screening	O					
Randomization		O				
Intervention						
Intervention group: TEA + EA		O	O	O		
Control group: EA		O	O	O		
Assessments						
Sunnybrook facial grading system	O	O		O	O	O
Facial disability index^*^		O		O	O	O
Numeric rating scale for stiffness		O		O	O	O
Synkinesis assessment questionnaire		O		O	O	O
Patient global impression of change				O	O	O
Euro-Qol 5-dimension 5-level		O		O	O	O
Economic cost evaluation		O		O	O	O
Adverse event		O	O	O	O	O

* Primary outcome.

SPIRIT, standard protocol items: recommendations for interventional trials; TEA, thread embedding acupuncture; EA, electroacupuncture.

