### Participants

2.2

Applicants will evaluate each volunteer based on the admission and exclusion criteria. The assigned plan of each group will be explained in full to the volunteers by the research assistants, along with the study procedure and consent documents. After signing an informed consent form and accepting the study invitation, qualified individuals schedule a baseline evaluation.

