### Sample size calculation

2.4

The level of significance (*α*) is set at 0.05 (two-sided test). Type II error (*β*) is set at 0.2, with a test power of 80%. No clinical trial of thread embedding with the same design could be found through a literature review. Therefore, the sample size was calculated by applying the mean difference of 9.29 and the standard deviation of 17.146 for the Facial Disability Index’s Physical score as the primary efficacy evaluation indicator, based on the results of previously conducted, similar clinical trials on the sequelae of FNP (10).

Considering a dropout rate of 20% (11), 71 participants per group will be needed. A total of 142 participants will be assigned to the study: 71 persons per group, with 102 patients (51 in the TEA group, 51 in the control group) at the one medical center and 40 patients (20 in the TEA group, 20 in the control group) at the other medical center. If an institution’s recruitment ends early, additional participants will be recruited competitively to ensure a smooth enrollment process.

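### The screening Sunnybrook rating appears to go unused in the between-arm comparison of the only evaluator-blinded efficacy outcome; as a second covariate beside Week 1 it could add some precision at almost no cost

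*Protocol article*

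**What the plan says.** All references are to the protocol article.

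- **Schedule.** In Table 1 (section 2.1) the row "Sunnybrook facial grading system" is marked at Screening, Week 1, Week 6, Week 8 and Week 16. No other outcome is marked at Screening. The Week 1 column carries the baseline label.
- **Pre-treatment point.** The abstract makes change in Sunnybrook a secondary outcome and gives one pre-treatment time: "Assessment points include before treatment (Week 1), after treatment completion (Week 6", followed by Weeks 8 and 16.
- **Order of visits.** Section 2.2 says that, after consent, "qualified individuals schedule a baseline evaluation". This suggests that screening and Week 1 are separate occasions, but no interval is given.
- **Eligibility.** Section 2.2.1 uses Sunnybrook twice: a total of at most 80, and a synkinesis criterion.
- **Blinding.** Under 2.6 the evaluator is blinded, and participants and interventionists are not. Under 2.8.2 the evaluator scores Sunnybrook. The other efficacy scales in 2.8 are reported by the participant.
- **Analysis.** Section 2.9 names the independent t-test or Wilcoxon rank-sum test between groups, with no covariate. It adds paired tests within each group and a repeated measures ANOVA whose time points are not listed.

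**The concern.** If the schedule is followed, every randomised participant has two Sunnybrook ratings made before treatment. The first must exist for everyone, because eligibility depends on it. A graded clinical score carries rating noise, and a second pre-treatment reading tells the analysis more about the participant's underlying level. The tests named in 2.9 have no place for it.

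This matters more for Sunnybrook than for an ordinary secondary outcome. The primary outcome is self-reported by participants who know their allocation, so the blinded rating is the main check on whether an observed difference reflects expectation. A wider interval than necessary weakens that check. What is at stake is precision on one secondary outcome, not bias.

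**Working it through.** **Figures in the article.** There is no Sunnybrook standard deviation, correlation or power target to reproduce. The only sample-size figure concerns the Facial Disability Index physical score, using "the mean difference of 9.29 and the standard deviation of 17.146". The normal formula 2(1.96 + 0.84)²(17.146/9.29)² gives 53.5, so 54 per arm, and the exact t-test needs 55. With 20% dropout, 55/0.8 = 68.75, so 69 against the stated 71. That is close, and it has no bearing on this point.

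**Assumed inputs.** R is the correlation between the screening and Week 1 ratings. r is the correlation of each of them with the follow-up rating, taken as equal for both at first. Variances are in units of the score variance.

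1. ANCOVA on Week 1 alone leaves residual variance 1 − r².
2. ANCOVA on both ratings leaves 1 − 2r²/(1 + R).
3. Reduction of the second relative to the first:

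| R | r = 0.6 | r = 0.7 | r = 0.8 |
|---|---|---|---|
| 0.80 | 6.3% | 10.7% | 19.8% |
| 0.90 | 3.0% | 5.1% | 9.4% |
| 0.95 | 1.4% | 2.5% | 4.6% |

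For example, at R = 0.9 and r = 0.7: 1 − 0.49 = 0.510; 1 − 0.98/1.9 = 0.484; 0.484/0.510 = 0.949. The standard error falls by about 2.6% (√0.949 = 0.974).

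4. **Separating two steps.** An unadjusted test on change from Week 1 has variance 2(1 − r) = 0.60 at r = 0.7. Adjusting for Week 1 takes this to 0.51, a fall of 15%. The screening rating then takes it to 0.484. Only the last step is the gain claimed here.

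5. **Unequal correlations.** Let w be the Week 1 and s the screening correlation with follow-up. The residual variance with both covariates is 1 − (w² + s² − 2wsR)/(1 − R²). At R = 0.8, w = 0.7:
   - s = 0.6: 1 − 0.178/0.36 = 0.506, against 0.51 (0.9% lower);
   - s = 0.5: 1 − 0.18/0.36 = 0.50, against 0.51 (2% lower);
   - s = Rw = 0.56: 1 − 0.1764/0.36 = 0.51, no gain.

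   An added covariate cannot raise the underlying residual variance. Its cost is one degree of freedom: with 142 participants, 139/138 = 1.007, or about 0.7%. The 0.9% case is therefore roughly break-even.

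6. **Averaging instead.** The variance of change from the mean of the two ratings is 1 + (1 + R)/2 − (w + s), against 2 − 2w from Week 1. Averaging helps only if w − s < (1 − R)/2. At R = 0.8, w = 0.7, s = 0.6 it gains nothing (0.60 against 0.60); with s = 0.5 the variance is 17% higher (0.70 against 0.60).

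7. **Effect of the cut-off at 80.** This was simulated with equal correlations (R = r), means 50 to 70, SD 12 to 15 and r = 0.6 or 0.8, all assumed. An averaged baseline produced a spurious within-arm change of 0.02 to 1.3 points; Week 1 alone gave about 0. The covariate gain remained, at 9.5% to 19.5%.

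**The case against.** The strongest reply is that nothing here is wrong or contradictory. Using the last pre-treatment visit as baseline is standard. It is also sensible when the screening value was used to select participants, because it keeps regression to the mean out of the paired tests in 2.9. How baseline is derived when two readings exist is commonly left to a full protocol or SAP, and neither is shown.

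Much of this stands. A reader might infer that the plan discards the screening rating. The article does not say so: it prints no rule for deriving Sunnybrook change, and only the labels and the named tests point that way. Nor does it say that the same evaluator makes both ratings, or exclude a screening score being carried forward to Week 1. In that last case R = 1 and the gain is nil.

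A reader might also infer that averaging the two ratings is the obvious remedy. It is not, because its gain can vanish or reverse and it would bias the planned within-arm tests. The objection does not reach the covariate form: there Week 1 can remain the within-arm baseline, and randomisation keeps the between-arm contrast free of selection bias.

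**Conclusion.** The point holds as an optional gain in efficiency. On the natural reading, a rating already collected is left out of the between-arm comparison of the one blinded efficacy outcome. Under the assumed correlations, including it removes about 1% to 20% of residual variance beyond Week 1 adjustment alone, and 5% in the middle case. The gain is near zero if the screening rating adds little to Week 1 or simply is the Week 1 value.

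Two stronger readings are not supported. The gain should not be expressed as extra participants out of 142, because that number was sized on the Facial Disability Index and Sunnybrook has no power target. Nor is there ground for calling the Week 1 rating compromised because it shares a visit with randomisation: the abstract places it before treatment and the evaluator is blinded. The primary outcome and the sample size are untouched.

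**What to change.** In 2.9 (or the SAP, before any unblinded analysis) state that between-arm comparisons of Sunnybrook at Weeks 6, 8 and 16 will use ANCOVA with the Week 1 and screening ratings both entered as covariates. State also that Week 1 alone remains the baseline for within-arm change and that the two ratings will not be averaged. If the screening score may be carried forward to Week 1, say so; the second covariate then has no purpose for those participants.

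The cost is a sentence or two and one degree of freedom, with no new visit, data or burden on participants.

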### Participants

2.2

Applicants will evaluate each volunteer based on the admission and exclusion criteria. The assigned plan of each group will be explained in full to the volunteers by the research assistants, along with the study procedure and consent documents. After signing an informed consent form and accepting the study invitation, qualified individuals schedule a baseline evaluation.

#### Inclusion criteria

2.2.1

Participants will be included if they meet the following criteria: (1) Adults aged between 19 and 80 years old, (2) Peripheral facial palsy more than 12 months after onset, (3) 80 points or less in a total score by the Sunnybrook Facial Grading System, (4) Synkinesis in more than one facial region by the Sunnybrook Facial Grading System, (5) Not receiving any treatment for the peripheral facial palsy sequelae within the last month, (6) Voluntary participation with written consent after hearing an explanation of the clinical trial.

#### Exclusion criteria

2.2.2

Participants will be excluded if they meet the following criteria: (1) Thread embedding acupuncture or botox treatment on the face within the last 3 months, (2) Hypersensitivity to electroacupuncture or thread embedding acupuncture, metal allergy, severe keloid skin, and other skin sensitivities, (3) Bilateral peripheral facial palsy sequelae, (4) Facial paralysis due to cerebrovascular disease, (5) Intracranial tumor around the facial nerve that was not removed, (6) Skin diseases or blood clotting disorders for which thread embedding acupuncture is contraindicated, (7) Pregnant or planning to become pregnant, (8) Mental illness or inability to communicate in compliance with clinical trials, (9) Other reasons judged unsuitable by the researcher.

### Criteria for withdrawal and termination

2.3

In accordance with ethical principles protecting patient autonomy, participants will have the right to withdraw from the study at any time and for any reason. The study may be discontinued in cases of consent withdrawal by the participant, the presence of a medical condition that endangers the participant’s safety, or the investigator’s determination that further participation is inappropriate for other reasons. I n the event of a severe adverse reaction, the investigator will permanently discontinue the clinical trial for the affected participant.

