#### Adverse events

2.8.8

Adverse reactions will be collected through research participants’ symptom reporting and researchers’ observations and will be identified by the frequency of occurrence between groups. Researchers will evaluate the causal relationship between each treatment method and the adverse effects experienced using a 6-point scale (18). (1 = related, 2 = probably related, 3 = possibly related, 4 = probably not related, 5 = definitely not related, and 6 = unknown) Moreover, all adverse effects will be classified into three levels according to Spilker’s classification method (19). (Mild (1): No treatment is required, and the participant’s daily life (function) is not significantly impaired; Moderate (2): The participant’s daily life (function) is significantly impaired, and treatment may be needed, but the condition improves after treatment; Severe (3): Severe adverse reactions require extensive treatment and may leave sequelae.)

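### Section 2.3 ends the trial for a participant after a severe adverse reaction without separating stopping treatment from leaving follow-up: a minor weakness in safety follow-up that is cheap to correct

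*Protocol article*

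**What the plan says.** Section 2.3 (Criteria for withdrawal and termination) covers participant withdrawal, discontinuation for safety, and the investigator's "determination that further participation is inappropriate for other reasons". It closes with a mandatory rule for severe adverse reactions: "the investigator will permanently discontinue the clinical trial for the affected participant". It has no category for someone who stops thread embedding acupuncture (TEA) or electroacupuncture but stays under observation.

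Section 2.8.8 (Adverse events) sets the top grade of its three-level scale as follows: "Severe adverse reactions require extensive treatment and may leave sequelae". Events are gathered from participants' reports and researchers' observations and "will be identified by the frequency of occurrence between groups".

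Table 1 ("SPIRIT schedule of the study") places adverse-event assessment at every visit from Week 1 to Week 16. It places the FDI at baseline and at Weeks 6, 8 and 16, with Week 8 as the primary endpoint. Section 2.9 keeps everyone treated at least once in the full analysis set (FAS) and multiply imputes missing values.

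**The concern.** What the rule discontinues is the clinical trial, not the treatment, and the section around it is about withdrawal and continued participation. The plain reading is that the participant leaves the study and the remaining scheduled visits lapse. No other part of the article keeps such a person under assessment.

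This matters mostly for safety, which the trial sets out to confirm. A participant with a reaction that may leave lasting damage is the one whose later course is most worth recording, and the scheduled visits are where recovery or sequelae would be documented. Because groups are compared on event frequency, a participant removed early also has fewer scheduled occasions on which later events can be counted. On the efficacy side, that person stays in the FAS, so FDI values that could have been observed would be imputed.

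**Working it through.** The article gives no figure on this point, so there is none to reproduce. The checks below size the loss on the plain reading.

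**1. Scheduled assessments lost (Table 1).** Adverse-event assessments fall at Week 1, Weeks 2–5 (four visits), Week 6, Week 8 and Week 16: 1 + 4 + 1 + 1 + 1 = 8. For a severe reaction at the session in week k (k = 1 to 6), the event is recorded at that visit and the rest are lost:

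- Adverse-event assessments lost = 8 − k, so 7 at Week 1 and 2 at Week 6.
- Weeks of follow-up lost = 16 − k, so 15 at Week 1 and 10 at Week 6.
- Post-baseline FDI assessments lost = 3 of 3 for k = 1 to 5. For k = 6 it is 2 or 3, depending on whether the Week 6 FDI is taken before or after that session.

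A reaction first seen at Week 16 loses nothing scheduled.

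**2. How often it might arise.** The article states no rate of severe reactions. With an assumed rate p in both arms, the chance of at least one case among 142 is 1 − (1 − p)^142 and the expected number is 142p:

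| Assumed p | Chance of at least one | Expected cases |
|---|---|---|
| 0.5% | 51% | 0.7 |
| 1% | 76% | 1.4 |
| 2% | 94% | 2.8 |

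These rates are illustrations with no source in the article. Applying them to the electroacupuncture-only arm as well raises the totals.

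**3. Effect on the primary estimate.** Inputs from section 2.4 are SD 17.146 and 71 per group. The standard error of the group difference in an imputed FAS, ignoring added imputation variance, is 17.146 × √(2/71) = 2.88. If one participant's imputed value is wrong by D points, that arm's mean moves by D/71. D is assumed; 9.29 is the planning difference in section 2.4.

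- D = 9.29: 0.13 points, 5% of the SE.
- D = 20: 0.28 points, 10% of the SE.
- D = 30: 0.42 points, 15% of the SE.

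These are not bounds. The shift can go either way and is zero if no case occurs.

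**4. Effect on power.** After 20% dropout, 71 × 0.8 = 56.8, about 57 per arm. Using Φ(9.29/SE − 1.96):

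- 57 and 57: SE = 17.146 × √(2/57) = 3.21, power 82.4%.
- 56 and 57: SE = 17.146 × √(1/56 + 1/57) = 3.23, power 82.1%.

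**5. Timing.** Section 2.1 says "The enrollment is expected to begin on June 22, 2023 and end on July 31, 2025". For someone enrolled on the last day, the Week 6 session is 5 weeks later, about September 4, 2025. The Week 16 visit is 15 weeks later, about November 13, 2025, one day after publication on November 12.

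**The case against.** The strongest reply is that a condensed article is being read too literally. The approved protocol, version 1.5, is not shown and may well provide for follow-up after treatment stops. The wording of section 2.3 is loose throughout: it speaks of the study being discontinued when one person withdraws consent, which cannot be meant literally. A treatment-only reading is therefore possible. Section 2.8.8 does not confine symptom reporting to scheduled visits, and its grades depend partly on how the condition evolves, which implies some knowledge of its course. The severe reaction itself would be counted in any case.

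Severe reactions also look rare. The Introduction cites a review of Korean facial thread embedding that found no significant side effects beyond mild bruising. It also cites a systematic review with no serious events for the polydioxanone thread mostly used in Korea, although serious is not the same as the severe grade in section 2.8.8.

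Much of this stands, and it makes the point small. It does not remove it. The article states a rule rather than leaving one out, and the words of that rule end the trial for the participant. Section 2.8.8 does not say that collection of reports continues afterwards. If version 1.5 separates the two decisions, the article misstates it and the sentence still needs correcting.

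A reader might go further and infer that the rule biases the primary result, perhaps towards TEA because only that arm can have TEA-caused reactions. The article does not support that: it gives no event rates by arm, no direction follows, and the shift per case is a small fraction of the standard error. Nor does it show that any participant has actually been lost in this way.

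**Conclusion.** The point holds as a minor one. Section 2.3 fixes the rule badly: on its plain reading, a severe reaction at a treatment session ends 2 to 7 of 8 adverse-event assessments and 2 or 3 of 3 post-baseline FDI assessments for a participant whose later course is of most safety interest. The harm is to safety follow-up, in probably very few people. The effect on the primary comparison is negligible and its direction unknown.

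The counts of lost visits follow from Table 1, given the plain reading. The case probabilities and the shifts in the arm mean rest on assumed values. Confidence is medium, because the treatment-only reading remains open and the full protocol is not shown.

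**What to change.** Reword section 2.3 so that a severe adverse reaction permanently stops study treatment only. Unless the participant withdraws consent to follow-up, keep the scheduled assessments at Weeks 6, 8 and 16, follow the reaction until it resolves or stabilises, and analyse the participant in the assigned group.

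On the stated dates the rewording can save almost no remaining visits. The useful step now is to identify anyone discontinued for a severe reaction, obtain their later status where consent allows, and report it.

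The cost is one reworded section, notice to the Ethics Committee (section 2.1: "If there are any changes in the study design, the Ethics Committee will be immediately informed"), and at most a few contacts per affected participant. The downside is asking people who stopped treatment after a bad reaction to attend or be contacted again.
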